#### Training resistance

To determine starting resistance (color of resistance band) a 25 RM shoulder flexion test will be performed, standing using the dominant arm, during baseline tests. The exercise movement will be instructed orally and visually by the primary investigator (AN). The following familiarization strategy will be used: 25 repetitions will be performed with the non-dominant arm using the lowest level of resistance (tan elastic band) to familiarize the patient with the exercise movement [37]. During familiarization, the patient will receive instructions to perform the exercise accurately - arm kept straight (elbow extended) throughout the whole movement holding the band in full can position with thumb pointing upwards; lifting the arm upwards/forward until the elbow passes the patient’s chin returning to the start position in a controlled manner with the same speed [27]. Length of the elastic band will be 1 m, stretched 25% at the start and proximally 75% at the end position, that is 1.75 m at the end position. During the test the patient will be instructed to perform as many repetitions as possible, and no additional feedback or encouragement will be provided. The 55% of peak value obtained during isokinetic shoulder flexion will be obtained and the elastic resistance band closest to this value at 75% elongation will be used. A change of elastic band results in a weight difference of 20 to 30% [28], and between 20 and 30 repetitions are considered 25 RM. The number of attempts needed to reach 25 RM will be recorded. Five minutes rest between attempts will be provided if necessary. Rating of muscle fatigue and dyspnea after each exercise using BORG CR10 will be recorded for each participant randomized to the intervention group.

### Sample size

A sample size of 17 in each group (intervention, control) will be required to obtain the power to detect a significant difference in lower limb local muscular endurance capacity measured by the 6-MWT [53]. The sample size calculation was made with the following assumptions: a relevant mean difference of 50 meters walked in 6 minutes with a standard deviation (SD) of 52, α = 0.05, β = 0.20 (80% power); and a two-tailed test of significance, based on a study by Costi and colleagues [54] (a RCT published in 2009 on unsupported training in patients with COPD). For QoL, the sample size calculation was made with these assumptions: a relevant mean difference of 1 unit (SD 1.07) on the Swedish version of the CRQ, α = 0.05, β = 0.20 (80% power); and a two-tailed test of significance, data based on CRQ values obtained in the study by Lacasse and colleagues [75] gave 17 patients in each group. Multicenter trials involve a correlation in data - subjects from the same center are likely to be more similar than subjects from other centers. Because such a correlation potentially affects the power of the data within the trial, the sample size needs to be adjusted, often increased, to account for the design of the study - in other words, the design effect [76]. Several considerations have been made to minimize the effect of using different centers: the same inclusion criteria for participants at all locations; specified and similar inclusion criteria for physiotherapists at all locations; standardized training for all physiotherapists to uniformly deliver the intervention; all aspects of the intervention regimen are standardized; a standardized exercise protocol will be given to both physiotherapists leading interventions and participants; physiotherapists give informed consent to follow the standardized instructions regarding the standardized patient education material; and exercise protocol and primary outcome measures are measured by the same (blinded) outcome assessor at all centers during pre- and post-tests. In addition, in an individually randomized trial, stratified for centers, the design effect is estimated to be < 1 which involves a gain in power, allowing a reduction in sample size rather than an increase [76,77]. With regard to the design of the study and the considerations taken to minimize the effect of using different centers, no adjustment of sample size will be made due to design effect. Nevertheless, the sample size is adjusted for potential drop-outs. We expect a drop-out rate of 20% based on a previous systematic review [78]. We aim to recruit five additional patients to each group, resulting in a total number of 44 patients, 22 in each group (17/0.8 = 21.3 ≈ 22) with moderate to very severe COPD. The total study group will consist of an equal number of males and females.

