
### Randomization and blinding

To prevent knowledge of treatment assignment and to keep the allocation sequence concealed from the participants and the researchers, group allocation will be completed after baseline and the inclusions tests performed by an individual independent of the recruitment process. This person will, after enrollment of participants, be emailed participation details and then perform the randomization using a randomly permuted blocks design with a computer random number generator (http://www.randomization.com). Randomization will be stratified by center and gender with a 1:1 allocation to the intervention or control group using random block sizes. The assignment to groups after randomization will be performed by a third party independent of the recruitment process for allocation and randomization. After randomization the allocation sequence will be kept in an opaque, sealed and stapled envelope, locked away in a safe deposit box at the department of Community Medicine and Rehabilitation, Physiotherapy, Umeå University, Umeå, and will be kept concealed until the end of outcome assessment. The envelope will be made impermeable to intense light by using aluminum foil inside and sealed using tamper-proof labels. Furthermore, the participants will be given repeated instructions not to reveal their group allocation to the outcome assessors during post-tests after the end of the intervention period. In case of a failure in keeping the outcome assessor blinded (that is, a patient reveals his/her group allocation) a second trained outcome assessor will be available to step in and conduct the post-tests.

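### The stated CRQ inputs give 18 completers per arm by the formula that reproduces the walk-test figure, not 17; a minor slip that leaves nominal CRQ power just under 80%

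*Protocol article*

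**What the plan says.** The CRQ is one of three primary outcomes (Primary outcomes). The Sample size section gives two calculations.

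- **6-minute walk test:** "a relevant mean difference of 50 meters walked in 6 minutes with a standard deviation (SD) of 52", with "α = 0.05, β = 0.20 (80% power); and a two-tailed test of significance". The stated result is 17 in each group.
- **CRQ:** "a relevant mean difference of 1 unit (SD 1.07) on the Swedish version of the CRQ", with the same alpha, power and sidedness. The section says that this "gave 17 patients in each group".

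The section then allows for drop-out ("We expect a drop-out rate of 20% based on a previous systematic review") and reaches a total of 44, "22 in each group (17/0.8 = 21.3 ≈ 22"). Allocation is 1:1 (Randomization and blinding). The Statistics section plans linear mixed models on all randomized patients, adjusted for baseline value, center and gender. The article does not name the sample-size formula.

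**The concern.** The two calculations share alpha, power, sidedness and allocation. They differ only in the ratio of SD to difference: 52/50 = 1.04 for the walk test and 1.07/1 = 1.07 for the CRQ. The required number grows with the square of that ratio, and the walk-test requirement already sits just under 17, so the CRQ should need more than 17. One number is nevertheless given for both.

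At stake is whether the 80% power stated for a primary outcome follows from its own inputs, and whether the recruitment target, which rests on 17 alone, covers the more demanding of the two calculations.

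**Working it through.** **Inputs** (all from Sample size, except 1:1 allocation from Randomization and blinding): two-sided alpha 0.05, so z = 1.960; 80% power, so z = 0.8416; walk test 50 m, SD 52; CRQ 1 unit, SD 1.07; drop-out 20%.

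**1. Reproduce the walk-test figure.** Normal approximation, per arm: n = 2 × ((1.960 + 0.8416) × SD / difference)².

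- 2 × (2.8016 × 52/50)² = 16.98, rounded up to **17**. This matches the protocol and points to the normal approximation as the method used. A two-sample t-test would need 18 (power 80.0% at 18).

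**2. Same formula, CRQ inputs.**

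- 2 × (2.8016 × 1.07/1)² = 17.97, rounded up to **18**, not 17.
- By t-test (noncentral t), power is 77.8% at 18 and 80.0% at 19, so **19**.
- A one-sided normal calculation gives 15, so that does not explain 17 either.

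**3. Can one rounding rule give 17 for both outcomes?**

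| Method | Rule | Walk test | CRQ |
|---|---|---|---|
| Normal | up or nearest | 17 | 18 |
| Normal | truncate | 16 | 17 |
| t-test | up | 18 | 19 |
| t-test | truncate | 17 | 18 |

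None does. The CRQ figure is what results if 17.97 is cut to 17 while 16.98 is rounded up.

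**4. Carry through the protocol's drop-out step.**

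- 17/0.8 = 21.25, so 22 (as stated)
- 18/0.8 = 22.5, so 23 per arm, 46 in total
- 19/0.8 = 23.75, so 24 per arm, 48 in total

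**5. Unadjusted CRQ power.** Normal approximation: Φ(√(n/2)/1.07 − 1.960). At n = 17 this is Φ(2.725 − 1.960) = Φ(0.765) = 77.8%. The planned recruitment implies 22 × 0.8 = 17.6 completers, where it is Φ(2.772 − 1.960) = Φ(0.812) = about 79%.

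| Per arm with outcome | Normal | t-test |
|---|---|---|
| 17 | 77.8% | 75.3% |
| 17.6 (expected) | about 79% | about 77% |
| 18 | 80.1% | 77.8% |
| 19 | 82.1% | 80.0% |
| 22 (no drop-out) | 87.3% | 85.7% |

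**6. Baseline adjustment.** Suppose that 1.07 is an unadjusted SD and that the baseline–outcome correlation r is 0.3 to 0.5 (an assumption; the article gives no value). The residual SD is then 1.07 × √(1 − r²), and power at 17 per arm is about 81% to 88% (normal) or 79% to 86% (t-test).

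**The case against.** The case for leaving this alone is that it is a one-patient rounding slip with almost no consequence. Most of that stands. On the protocol's apparent method the gap is one patient per arm. Rounding 21.25 up to 22 leaves 17.6 expected completers, which absorbs more than half of it. The planned analysis also adjusts for baseline, which the sample-size calculation does not use and which could bring power to 80% or above.

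Two limits apply. First, adjustment does not make the stated inputs yield 17, and its gain is uncertain: the article does not say whether 1.07 is the SD of a raw score or of a change score, and the gain would differ if it is the latter. Second, including all randomized patients in the mixed model does not by itself secure the power shown for 22 per arm. There is one post-test (Screening tests and outcome assessment), so in a model with baseline as a covariate a patient who misses it adds essentially nothing to the treatment comparison.

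A reader might go further and infer that the trial delivers only about 75% power for quality of life. The documents do not support that. The 75% figure requires an unadjusted t-test with exactly 17 completers; the article names no such test, expects 17.6 completers, and plans an adjusted model. About half of the apparent five-point shortfall comes from switching to the t distribution. A reader might also infer that the walk-test figure is wrong because a t-test needs 18. It is not: 17 is right under the normal approximation, and choosing between two accepted methods does not expose an error.

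**Conclusion.** Wrong as written, and minor. No standard two-sided calculation turns the stated CRQ inputs into 17; they give 18 by the method that fits the walk-test figure and 19 by t-test. The recruitment target inherits the slip: 22 per arm where the protocol's own step would give 23.

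The shortfall in nominal power is roughly one to two points on the normal approximation (79% at the expected completers, 78% at 17), or three to five by t-test (77% and 75%). These figures assume the stated difference and SD, equal arms, 20% drop-out and no covariate adjustment. The planned adjustment may close the gap, by an amount that the article does not allow one to fix. What is certain is the arithmetic, 18 against 17; the power that the trial will actually have is not.

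**What to change.** In the Sample size section:

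- Change the CRQ requirement to 18 completers per arm, naming the normal approximation (19 if a t-test is used).
- Keep 22 recruits per arm and state the nominal unadjusted CRQ power: about 78% at 17 completers per arm (75% by t-test), or about 79% (77% by t-test) at the expected 17.6. Note that the planned adjustment for baseline may raise it.
- Leave the walk-test figure of 17 unchanged.

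The cost is about one corrected sentence and a stated CRQ power slightly below 80%; recruitment does not change.

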
### Randomization and blinding

To prevent knowledge of treatment assignment and to keep the allocation sequence concealed from the participants and the researchers, group allocation will be completed after baseline and the inclusions tests performed by an individual independent of the recruitment process. This person will, after enrollment of participants, be emailed participation details and then perform the randomization using a randomly permuted blocks design with a computer random number generator (http://www.randomization.com). Randomization will be stratified by center and gender with a 1:1 allocation to the intervention or control group using random block sizes. The assignment to groups after randomization will be performed by a third party independent of the recruitment process for allocation and randomization. After randomization the allocation sequence will be kept in an opaque, sealed and stapled envelope, locked away in a safe deposit box at the department of Community Medicine and Rehabilitation, Physiotherapy, Umeå University, Umeå, and will be kept concealed until the end of outcome assessment. The envelope will be made impermeable to intense light by using aluminum foil inside and sealed using tamper-proof labels. Furthermore, the participants will be given repeated instructions not to reveal their group allocation to the outcome assessors during post-tests after the end of the intervention period. In case of a failure in keeping the outcome assessor blinded (that is, a patient reveals his/her group allocation) a second trained outcome assessor will be available to step in and conduct the post-tests.

### Statistics

The analysis of primary and secondary outcome measurements will include all randomized patients. To be able to use all patient data, the mixed models approach will be adopted with individuals at level one and center at level two. The analysis will demonstrate any improvements at follow-up, comparing the intervention and control group. In linear mixed models the variable group is considered main, controlling for baseline value, center and gender. To judge the quality of the model we will analyze the residuals. A difference at the *P* < 0.05 level will be considered significant in all outcome measures and analyses. For each outcome the results will be reported as a summary of the outcome in each group presented as mean and SD, together with effect size. For treatment effect, 95% confidence intervals (CI) and *P* values will be presented. For each group, information about the number of participants included in each separate analysis and whether theses analyses were by original assigned groups will be given. Correlation between changes in physical variables and changes in health variables will be measured by Pearson correlation. A pre-specified subgroup analysis of participants randomized to the intervention group will be performed to investigate differences in BORG CR10 rating between elastic resistance exercises to evaluate the strength relationship between involved muscles/movements. Our research group has previously found relatively lower thigh muscle strength in female patients with COPD compared to male patients with COPD and healthy controls [32]. In addition, Skumlien and colleagues [79] found gender differences regarding effects following a pulmonary rehabilitation program and further research regarding the potential differences in training effects between female and male patients with COPD is required. Therefore, we aim to compare primary and secondary outcome measures for males versus females in pre-specified subgroup analyses to gather information for future studies. Intention-to-treat analysis will be used for all outcome measurements and involve all patients who are randomly assigned. Mixed models will be used to handle missing outcome data. In addition, within the main analysis, an on-treatment analysis will be executed. On-treatment is defined as at least 80% compliance - in other words, at least 20 training sessions or three education sessions depending on group allocation. For data management and statistical analysis the IBM Statistical Package for Social Sciences (SPSS) version 20.0 will be used.

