### Screening tests and outcome assessment

Different tests will be performed before the start of the study and directly after the 8-week intervention period at Norrlands University Hospital, Umeå, and Karolinska University Hospital, Huddinge. Participants at Örnsköldsvik Hospital, Örnsköldsvik, will perform tests at Norrlands University hospital, Umeå, due to lack of specific test equipment. The primary outcome measures will be assessed by the same researcher (AN) for all participants at each location. Pre-tests will be performed on four occasions, within 3 weeks, before the start of intervention, and post-tests will be performed on three occasions within 2 weeks. Each test occasion will last from 1 to 2 h. Pre- and post-tests will be performed at the same time of day, with the same rest between test occasions and during tests. Since a subject's motivation may determine attainment of maximal effort [7], both pre- and post-tests are performed using standardized information and encouragement [32]. No additional follow-up apart from directly after the end of the intervention period is used within this trial. However, previous studies show that the benefits of exercise training on exercise capacity and QoL in patients with COPD appear to decline by 12 to 24 months despite different exercise strategies [40,41]. There is an urgent need to find effective strategies on how to maintain the positive effects for a longer period. Therefore, in connection with the study described in this protocol, a randomized controlled study is planned to evaluate the effect of motivational interviewing as a strategy to maintain/increase the level of physical activity after a training program (and by that also the benefits achieved from the training program). Participants randomized to the intervention group will be asked to participate, and follow-up tests will be performed at 6, 12 and 24 months. A trial protocol will be published with further description.

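### With one post-test per patient, the specified mixed model is in effect a complete-case ANCOVA, so the claims that it includes all randomized patients and handles missing outcomes are wrong

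*Protocol article*

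**What the plan says.** All the statements about the model are in the Statistics section of the protocol article.

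- **Analysis set:** "The analysis of primary and secondary outcome measurements will include all randomized patients" and "Intention-to-treat analysis will be used for all outcome measurements and involve all patients who are randomly assigned".
- **Missing data:** "Mixed models will be used to handle missing outcome data". The article names no other method.
- **Model levels:** "To be able to use all patient data, the mixed models approach will be adopted with individuals at level one and center at level two".
- **Covariates:** "In linear mixed models the variable group is considered main, controlling for baseline value, center and gender".

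Under Screening tests and outcome assessment, the number of outcome occasions is fixed: "No additional follow-up apart from directly after the end of the intervention period is used within this trial".

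The Sample size section states: "We expect a drop-out rate of 20% based on a previous systematic review". It raises 17 per group to 22, or 44 in total.

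**The concern.** A mixed model makes use of incompletely observed patients when several response occasions are nested within each patient, because the observed occasions then carry information about the missing one. The model here has no such level. The patient is the lowest unit, the baseline is on the covariate side, and there is only one later measurement. A random or fixed effect for center does nothing for a patient whose only response is absent.

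At stake is what a reader of the results would believe. The wording suggests that missing outcomes have been dealt with and that everyone randomized is in the estimate. In fact the estimate would come from patients who attended the post-test, under an assumption that is not stated. The assumption deserves attention because the arms ask different things of patients: 24 exercise sessions plus four education sessions, against four education sessions alone.

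**Working it through.** **1. Responses per patient.** Baseline is a covariate and there is one post-test, so each patient has one response row per outcome if the post-test was done, and none if it was not. This is so whether center is entered as a random level, a fixed effect or both.

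**2. The plan's own sample size.** Inputs from the Sample size section: difference 50 m, SD 52 (6MWT); difference 1 unit, SD 1.07 (CRQ); two-sided α 0.05; power 80%; drop-out 20%. Per-group size is 2 × [SD × (1.960 + 0.842) / difference]².
- 6MWT: 16.98, so 17, as stated.
- CRQ: 17.97, so 18, against 17 stated (one patient, immaterial here).
- Drop-out: 17 / 0.8 = 21.25, so 22 per group and 44 in total, as stated.

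**3. Patients expected in the analysis.** Assume that every drop-out misses the post-test: 44 × 0.80 = 35.2, or 17.6 per arm. About 35 are analysed and about 9 are not.

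**4. Power at 17.6 per arm.** The standard error of the 6MWT difference is 52 × √(2 / 17.6) = 17.5 m. Power is Φ(50 / 17.5 − 1.96) = 81% for the 6MWT and, in the same way, 79% for the CRQ. By t-test the values are 79% and 77%. Power is therefore not the problem.

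**5. Illustration by simulation.** One data set of 44 patients was generated with a true effect of 50 m and residual SD 52. The baseline mean of 400 m, baseline SD of 80 m and split across centers were assumptions. Nine post-tests were removed at random (four control, five exercise).

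| Model | Patients used | Estimate (m) | SE |
|---|---|---|---|
| As specified, center at level two | 35 | 55.4 | 13.7 |
| Complete-case ANCOVA, center fixed | 35 | 57.2 | 13.7 |
| Baseline and post-test nested in patient | 44 (79 rows) | 54.9 | 13.1 |

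The first two models use the same 35 patients and differ only in how center enters. The third admits everyone but hardly moves the result. That is expected: with one follow-up, a patient who has only a baseline informs the baseline mean and says almost nothing about the treatment effect.

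**6. What a missing-not-at-random analysis could show.** Suppose completers differ by 50 m, and a fraction m of the exercise arm lacks a post-test and is given the control-arm change. The effect becomes (1 − m) × 50: 45 m at 10%, 40 m at 20% and 35 m at 30%. These are illustrations. The documents give one overall drop-out rate and none by arm.

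**The case against.** The best defence is that the specified model is a respectable analysis. It conditions on group, baseline, center and gender and is valid if outcomes are missing at random given these. Drop-out that merely differs by arm does not bias it. Recasting the model with occasions within patients changes almost nothing, as the table shows. Analysis by assigned group is kept, and the Statistics section promises to report the number of participants in each analysis, so any shortfall would be visible. All of this stands. It shows that the estimate may be sound; it does not make the two claims true.

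Several stronger readings are tempting but not supported.

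- *A reader might infer that intention-to-treat is abandoned.* It is not. The separate on-treatment analysis implies that non-compliers stay in the main analysis, and a patient who stops training but attends the post-test is included.
- *A reader might infer that inflating 17 to 22 contradicts intention-to-treat.* It does not. Missing outcomes reduce information under any model, so allowing for them is sensible.
- *A reader might treat 35 of 44 as settled.* It is an expectation that equates drop-out with a missing post-test, and it may differ by outcome.
- *A reader might infer a known bias.* If poor responders leave the exercise arm only (assumed log-odds slope 0.8 per SD, about 20% loss), completers show about 57 to 58 m for a true 50 m. The same mechanism in both arms gives 49.9 m. Nothing in the documents selects one over the other. The offer of training to controls after post-tests may also help to keep them in.

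Finally, details of missing-data sensitivity analyses may sit in a fuller protocol or analysis plan that is not shown, so their absence from the article is not itself a fault.

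**Conclusion.** The point holds as a misstatement about the primary analysis. Given the model levels, the baseline covariate and the single post-test, patients without a post-test are outside the likelihood. The claims of including all randomized patients and of handling missing outcomes through the mixed model are wrong as written, and nothing else in the article repairs them. In effect the analysis is a complete-case ANCOVA under an unstated missing-at-random assumption.

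About 9 of 44 patients would be left out if all planned drop-outs miss the post-test, and fewer if some attend it. Power is essentially as planned. Bias arises if missingness depends on the unobserved outcome, particularly in the exercise arm. Its size cannot be determined from the documents. The on-treatment analysis gives no protection, because it selects patients further by compliance.

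**What to change.** 1. Replace the two claims with a description that is true of the model: *all randomized patients with a post-test, analysed by assigned group, assuming outcomes are missing at random given group, baseline, center and gender.* Alternatively, nest baseline and post-test occasions within participant so that every patient with a baseline enters, and say that with one follow-up this hardly changes the estimate.
2. State that post-tests will still be sought from patients who stop training. This is the most direct protection for the analysis set.
3. Unless a fuller plan already does so, pre-specify one missing-not-at-random sensitivity analysis for the three primary outcomes. One example is to impute exercise-arm patients without a post-test from the control-arm change.

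The cost is a few sentences, one additional analysis of data already collected, and a less favourable description of the analysis set. The change should be made before group allocation is revealed to the analysts.

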#### Secondary outcomes

1. Determine the effect of HRSLE on: 1) endurance time, ventilatory response, perceived dyspnea and leg fatigue during submaximal cycle test; 2) maximal strength and muscular endurance during isokinetic tests; and 3) self reported dyspnea, self-efficacy, anxiety and depression.

2. Determine the relationship between: 1) changes in self reported dyspnea, self-efficacy, anxiety and depression; and 2) changes in exercise capacity

3. Identify if there are any sex-related differences in exercise training effects.

4. Determine if this exercise regimen is feasible and safe in stage II-IV COPD patients.

5. Develop a strategy to minimize attempts needed to determine a multiple repetition resistance using elastic bands.

6. Develop a strategy to optimize resistance for each involved movement within an exercise regimen.

7. Investigate the relationship between muscle fatigue and dyspnea in the different exercise tests.

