#### Chronic dyspnea questionnaires

The Medical Research Council (MRC) Dyspnea scale is a five-point scale based on degrees of various physical activities that cause dyspnea [61] and will be used to grade the patients’ inconvenience. The MRC dyspnea scale has been used in numerous clinical trials involving COPD [62], and is shown to be valid in COPD patients [63].

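### The Pearson correlation planned for secondary outcome 2 has no term for randomized group, so if the arms are pooled, as the text implies, the treatment effect leaks into the coefficient

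*Protocol article*

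**What the plan says.** Item 2 under Secondary outcomes sets out to relate "changes in self reported dyspnea, self-efficacy, anxiety and depression; and 2) changes in exercise capacity". The analysis for it is one sentence in the Statistics section: "Correlation between changes in physical variables and changes in health variables will be measured by Pearson correlation".

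Three other statements in that section bear on how to read the sentence:

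- Primary and secondary analyses are to include all patients randomized, and the intention-to-treat statement later in the section repeats this.
- The treatment comparisons do carry a group term and covariates: "In linear mixed models the variable group is considered main, controlling for baseline value, center and gender". Nothing similar is said for the correlation.
- The sentence after the correlation confines a different analysis, of Borg ratings between exercises, to the intervention arm. The correlation has no such restriction.

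The section also applies the 0.05 significance level to all outcomes and analyses, which includes these correlations.

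**The concern.** A correlation of changes is of interest here because it might show that patients who gain more exercise capacity also gain more in symptoms or confidence. In a two-arm trial a coefficient over all patients has two sources: the association among patients within an arm, and the distance between the two arm means. If training moves both variables, the second source alone gives a non-zero coefficient. That part only restates the treatment effects already estimated under secondary outcome 1. The distortion grows with the treatment effect, so it is largest when the trial succeeds.

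What is at stake is the interpretation of one secondary objective. A pooled coefficient could be reported as a link between fitness gain and symptom gain when part or all of it is the contrast between trained and untrained patients.

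**Working it through.** **Inputs from the Sample size section.** For walking distance, "a relevant mean difference of 50 meters walked in 6 minutes with a standard deviation (SD) of 52"; for quality of life, "a relevant mean difference of 1 unit (SD 1.07) on the Swedish version of the CRQ"; with "α = 0.05, β = 0.20 (80% power") and "a two-tailed test of significance". The section gives 17 per group, raised to 22 per group for 20% drop-out. Allocation is 1:1.

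**Reproducing the plan's figures.** With n per group = 2(1.960 + 0.842)²(SD/difference)²:

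- 6-minute walk: 15.70 × (52/50)² = 16.98, so 17. This agrees.
- CRQ: 15.70 × (1.07/1)² = 17.97, so 18 against the stated 17. One patient per group is immaterial here.
- Drop-out: 17/0.8 = 21.25, so 22 per group and 44 in total. This agrees.

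The article gives no figure for the correlation analysis. A change needs both measurements, so between 34 patients (17 per group) and 44 (no drop-out) would contribute.

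**Formula.** Let each change have SD 1 within arms, let the arm means differ by d₁ and d₂, and let ρ be the within-arm correlation. With equal arms, pooling adds d²/4 to each variance and d₁d₂/4 to the covariance:

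r = (ρ + d₁d₂/4) / √[(1 + d₁²/4)(1 + d₂²/4)]

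**Planning effects, ρ = 0.** d₁ = 50/52 = 0.962 and d₂ = 1/1.07 = 0.935.

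- Numerator: 0.962 × 0.935 / 4 = 0.225
- Denominator: √(1.231 × 1.218) = 1.225
- r = 0.225/1.225 = 0.18

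**Range.** The article gives no expected effect for dyspnea, self-efficacy, anxiety or depression, so d₂ is an assumption and is varied. Its top value is the CRQ planning effect. Rejection rates come from 100,000 simulated bivariate normal trials per row, two-sided 0.05, d₁ = 0.962, ρ = 0.

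| Assumed d₂ | Expected pooled r | Significant, N = 34 | Significant, N = 44 |
|---|---|---|---|
| 0 | 0.00 | 5.1% | 5.0% |
| 0.2 | 0.04 | 5.6% | 5.8% |
| 0.3 | 0.06 | 6.5% | 7.1% |
| 0.5 | 0.11 | 9.1% | 10.5% |
| 0.935 | 0.18 | 18.4% | 22.8% |

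In the same simulated trials, the partial correlation adjusted for arm (N − 3 degrees of freedom) averaged 0.00 and was significant in 4.9 to 5.1% of them.

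**Hand check of the last row by Fisher's z.** atanh(0.183) = 0.186.

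- N = 34: the standard error is 1/√31 = 0.180, so the shift is 1.03. The chance of exceeding 1.96 is P(Z > 0.93) ≈ 18%.
- N = 44: the standard error is 1/√41 = 0.156, so the shift is 1.19 and P(Z > 0.77) ≈ 22%.

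**When there is a real within-arm association** (planning effects):

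- ρ = 0.30 appears as (0.30 + 0.225)/1.225 = 0.43.
- ρ = −0.20 appears as (−0.20 + 0.225)/1.225 = 0.02, so an inverse relation would be hidden.

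**The case against.** **Pooling is not stated.** The article does not say whether the arms are combined, and Pearson coefficients within each arm would fit the sentence. This stands as a limit on certainty. Even so, the all-patients statement, and the restriction placed on the next analysis but not on this one, make pooling the natural reading.

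**This is detail for the analysis plan.** A condensed article need not list covariates for an exploratory correlation, and the full plan may already adjust for group. If it does, the point falls away. But the article names a specific statistic, and read as written it has a defect that a different statistic removes. That goes beyond missing detail.

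**The objective asks only for a relationship.** Secondary outcome 2 mentions neither a within-arm association nor mediation, so an overall correlation is a literal answer. That is fair. Still, the overall coefficient mixes two things that a reader will want to keep apart, and one of them is already reported elsewhere.

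**The effect may be small.** This stands. With no effect on the health variable there is no distortion, and with effects up to 0.3 SD the error rate stays at about 7% or less.

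**Dyspnea scale.** A reader might also infer that Pearson is wrong for the MRC scale, which "is a five-point scale based on degrees of various physical activities that cause dyspnea". A rank-based coefficient is a reasonable preference for such a scale, but nothing in the article shows that Pearson would mislead for its changes. It forms no part of the point.

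**Conclusion.** The point holds as a minor one. If both arms are pooled, the planned coefficient is pulled towards the product of the two treatment effects. With zero within-arm correlation and the planned walking effect, the expected r is 0.00, 0.11 or 0.18 for health-variable effects of 0, 0.5 or 0.93 SD. The false-positive rate is 5%, 9 to 11% or 18 to 23%.

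A reader might infer that the analysis will find a relationship where none exists. The figures do not support that. Even at the largest of these effects, at least 77% of trials would show no significant correlation, and the expected artefact of 0.18 lies below the smallest significant |r| (0.34 with 34 patients, 0.30 with 44).

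The result rests on these assumptions:

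- The arms are pooled.
- The planning SDs are within-arm SDs of change.
- Data are normal and arms are equal in size.
- Scales are oriented so that improvement is positive.
- The CRQ effect is only a stand-in at the upper end for variables with no stated effect.

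The primary comparison has its own group term and is untouched.

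**What to change.** For secondary outcome 2, state that the association between the two changes will be estimated by the partial correlation adjusted for randomized group, or by combining the within-arm correlations, and reported with a 95% CI. If within-arm coefficients were intended all along, say so.

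The cost is one sentence and one degree of freedom. The data, visits and sample size stay the same, and no other analysis changes.
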